	**Organization of care**				
		Implementation of components of the TCM^d^	Economic benefits: cost calculations of comparison between control and intervention hospital readmissions from the index admission Includes TCM intervention cost compared with usual care cost		
		Implementation of the transition action plan for all patients	Customized transition action plan developed		

^a^ESAS: Edmonton Symptom Assessment System.

^b^GSE: General Self-Efficacy Scale.

^c^PCCQ: Patient Continuity of Care Questionnaire.

^d^TCM: transitional care model.

### Sample Size Estimation and Justification

We anticipate that the enrollment of approximately 200 patients over 15 months will be feasible and provide a sufficient sample size to achieve the primary outcome, with the anticipated baseline readmission rate in the control group and absolute reduction in the intervention group (Table 3). Enrollment commenced in February 2024 and was completed on March 31, 2025. Given that the primary end point will be derived from health information systems in South Australia and that the study has an intention-to-treat approach, there will be a need to consider a larger sample size, taking into account withdrawals, dropouts, or loss to follow-ups.

**Table 3 table3:** Sample size per group by baseline readmission rate and absolute reduction in readmission with 80% power (α=.05).

Absolute reduction in readmission rate in the intervention group (%)	Baseline readmission rate in the control group at 3 mo, n		
	35%	40%	45%
15	136	150	160
20	70	79	86
25	40	47	52

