## Methods

### Ethical Considerations

This project received ethics approval on June 29, 2023, from the CALHN Human Research Ethics Committee (17554). It was registered with the Australian New Zealand Clinical Trials Registry on February 15, 2024 (12624000142538). Written informed consent will be obtained from all participants to ensure that they understand the study requirements, risks, and benefits. If potential participants accept an invitation to participate in the study, they will be provided with a participant information sheet and consent form for consideration. They will then be approached 24 hours later to confirm their willingness to participate. The study commenced on July 1, 2023; data collection started in February 2024 and was completed on March 31, 2025. Finalized results are expected in March 2026.

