**Primary**					
	The percentage of patients having hospital re-presentation (emergency department presentation with or without hospital admission) within 3 months of discharge from the index admission			Re-presentation data available from the electronic medical record Statistical analysis: comparison of proportions between treatment and control groups and time to re-presentation analysis using the log-rank test with the method of Kaplan-Meier [55]	

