**Secondary**					
	**Health care use**				
		The rate of hospital re-presentation within 1, 6, and 12 months of discharge from the index admission	Readmission data available from electronic medical record Rate defined as the number of re-presentations over a unit of time (eg, 1 y) Statistical analysis: nonparametric comparison of rates of re-presentation between treatment and control groups		
		Overall length of hospital stay within 1, 3, 6, and 12 months of discharge from the index admission	Readmission data available from electronic medical record Defined as the cumulative number of days spent in hospital over a unit of time (eg, d/y) Statistical analysis: nonparametric comparison of rates of re-presentation between treatment and control groups		
		Cost of transition service	Economic benefits of the intervention will be confirmed through a comparison of subsequent rehospitalization costs in the treatment and control groups		

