## Results

This project received ethics approval (17554) on June 29, 2023, and it was registered with the Australian New Zealand Clinical Trials Registry on February 15, 2024 (12624000142538). This study commenced on July 1, 2023, with data collection commencing in February 2024; data collection was completed on March 31, 2025. Finalized results are expected in March 2026.

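### Enrolment and data collection are both dated as ending on 31 March 2025, which conflicts with the 3-, 6- and 12-month outcome windows, and final results in March 2026 leave no room for complete 12-month outcomes

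*Protocol article*

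**What the plan says.** Sample Size Estimation and Justification (protocol article) states: "Enrollment commenced in February 2024 and was completed on March 31, 2025". Ethical Considerations states: "data collection started in February 2024 and was completed on March 31, 2025. Finalized results are expected in March 2026". The Results section repeats that "data collection was completed on March 31, 2025", and the abstract gives the same dates.

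Table 2 measures the primary outcome, the percentage of patients who re-present, "within 3 months of discharge from the index admission". Among the secondary outcomes it lists "The rate of hospital re-presentation within 1, 6, and 12 months of discharge from the index admission", and cumulative length of stay at 1, 3, 6 and 12 months. All of these come from the electronic medical record.

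The Data Collection section names reviews of the electronic medical record as one of the ways in which data are gathered. No place in the article gives a separate end of follow-up or a later extraction date.

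**The concern.** Participants are recruited as inpatients, so index discharge falls on or after the day of enrolment, and every outcome window opens at discharge. A trial that stops recruiting and stops collecting data on the same day has no follow-up time left for its most recent patients.

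What is at stake depends on where the record extract actually stops. If it stops on the stated date, the comparison of proportions, which Table 2 lists first for the primary outcome, would count patients with short follow-up as having had no re-presentation. Both observed percentages would fall and the difference between them would shrink. Most 12-month outcomes would be incomplete.

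The expected date for final results raises a second, smaller conflict with the 12-month outcomes, wherever the extract stops.

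**Working it through.** **Inputs from the article.** Enrolment from February 2024 to 31 March 2025 (13 to 14 months); data collection ended 31 March 2025; final results March 2026; windows of 1, 3, 6 and 12 months from index discharge; about 200 patients, 1:1; index stays above 3 weeks excluded.

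**The article's own figure.** Table 3 is reproduced in all nine cells by n = (1.96 + 0.84)² × [p1(1 − p1) + p2(1 − p2)] / (p1 − p2)², two-sided. For 40% versus 20% this is 7.85 × (0.24 + 0.16) / 0.04 = 78.5, so 79 per group, as printed. The table is not in dispute.

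**Dates.** Counting forward from a last enrolment on 31 March 2025, and back from a data cut-off on that day:

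| Window | Last discharge with a full window by 31 March 2025 | Last patient's window closes, discharge 31 March 2025 | Same, discharge 21 days later |
|---|---|---|---|
| 1 month | 28 Feb 2025 | 30 Apr 2025 | 21 May 2025 |
| 3 months (primary) | 31 Dec 2024 | 30 Jun 2025 | 21 Jul 2025 |
| 6 months | 30 Sep 2024 | 30 Sep 2025 | 21 Oct 2025 |
| 12 months | 31 Mar 2024 | 31 Mar 2026 | 21 Apr 2026 |

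The final nurse consultation, 6 to 10 weeks after discharge (Intervention section), would also fall between 12 May and 9 June 2025 for a patient discharged on 31 March 2025.

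**Share of patients affected.** The article gives no accrual curve. Assume uniform accrual of 200 over 14 months, discharge on the day of enrolment, and a cut-off on 31 March 2025:

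- short of 3 months: 3/14 = 21%, about 43 patients
- short of 6 months: 6/14 = 43%, about 86 patients
- short of 12 months: 12/14 = 86%, about 171 patients

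If the first enrolment is placed anywhere from 1 to 29 February 2024 and days are counted, the ranges are 21–23%, 43–46% and 86–92%.

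**Effect on the comparison of proportions.** Assume a constant hazard over the 3 months. With a true 3-month risk p and h = −ln(1 − p), the expected observed proportion is (11/14) × p + (3/14) × (1 − p/h).

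- p = 0.40: h = 0.511; 0.3143 + 0.2143 × 0.2170 = 0.361
- p = 0.20: h = 0.223; 0.1571 + 0.2143 × 0.1037 = 0.179

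The difference shrinks from 20.0 to 18.1 points. With 100 per arm and a pooled two-sided test at 5%, the normal approximation gives power of 87.6% with full follow-up. With truncation it is Φ[(0.1814 − 1.96 × 0.0628) / 0.0615] = Φ(0.95) = 83%. For 45% versus 25% the observed proportions become 40.7% and 22.4%, and power falls from 85% to 80%.

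**The case against.** The strongest answer is that these outcomes accumulate passively in hospital records and can be pulled at any later date. The sample size section says that the primary end point comes from South Australian health information systems. It also gives enrolment the same dates that other sections give data collection, so the latter phrase may simply be a loose label for the recruitment period. Nothing in the article says that the record extract stopped on 31 March 2025.

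This stands as a limit on the conclusion. A reader might infer that the late patients' primary outcomes are lost; the documents do not support that. But the benign reading is not stated either, and it sits badly with the Data Collection section, which counts record reviews as data collection. It would also leave the March 2026 conflict in place.

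Three further points stand. Table 2 also plans Kaplan-Meier and log-rank for the primary outcome, which treat short follow-up as censored; in simulation under the same assumptions, log-rank power under truncation stays at about 84% (40% versus 20%) and 82% (45% versus 25%). Truncation by calendar date applies to both randomised arms, so it dilutes the difference and does not favour either arm. And the results date is only an expectation: it misses the last 12-month window by between zero and about three weeks, plus analysis time. It would be too strong to say that it precedes the 12-month follow-up of most patients.

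**Conclusion.** The conflict in the dates is certain and needs no assumption: recruitment and data collection cannot both have ended on 31 March 2025 if every patient is to have the 3-month primary outcome, and still less the 6- and 12-month outcomes. It is also clear that "Finalized results are expected in March 2026" cannot realistically cover complete 12-month outcomes, because the last window closes on 31 March 2026 at the earliest and extraction and analysis must follow.

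The harm is conditional. The shares of 21%, 43% and 86% rest on uniform accrual and a literal cut-off. The loss of about 5 points of power in the comparison of proportions rests in addition on a constant hazard, 100 patients per arm and the chosen event rates. In these two scenarios power remains about 80% or better, so the damage to the primary comparison would be modest; the damage to the 12-month outcomes would be large. If the records are extracted later, the primary outcome is unaffected and this reduces to a correction of stated dates.

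**What to change.** - State that 31 March 2025 is the close of recruitment, and correct the sentences in the abstract, Ethical Considerations and Results that call it the completion of data collection.
- Set the record-extraction dates relative to the last index discharge: at least 3 months after it for the primary analysis and at least 12 months after it for the final extract.
- Move the report of 12-month outcomes to after the final extract, or label the March 2026 report as covering the primary outcome and the 1-, 3- and 6-month outcomes only.

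The cost is a later record extract and a delay of weeks for the 12-month results. No further patient contact is needed, and Table 3 does not change.

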### Randomization

The randomization will occur at the individual level. The participants will be randomized 1:1, with stratification at the ward or unit level to intervention or control, using REDCap, a secure, web-based software platform designed to support data capture for research studies [53].

### Control

Participants in the control group will receive usual care, which is defined as the “usual follow-up services” planned while the patient is in hospital, before discharge. Transition care is not implemented after discharge from the hospital (usual care). Usual services are planned or initiated while the participant is in the hospital in preparation for discharge, but provision of these services is not followed up by the STARnurses.

### Eligibility Criteria

The eligible population includes individuals aged ≥18 years with multimorbidity who fulfill all inclusion criteria and do not meet any of the exclusion criteria. For the purposes of the inclusion criteria, multimorbidity is defined as the coexistence of 2 or more chronic conditions [56] (Textbox 1).

Inclusion and exclusion criteria.
**Inclusion criteria**
Inpatients (ward or emergency department)Sufficient cognitive function and English language skills to provide informed consent and complete assessmentsAbility to engage in telehealthA history of either diabetes with cardiovascular disease or comorbidity in minimum 3 of the following illness domains:Diabetes—type 1 or type 2Cardiovascular disease—symptomatic atherosclerotic disease (ischemic heart disease, cerebrovascular disease, peripheral vascular disease, symptomatic valvular heart disease, or atrial fibrillation)Chronic cardiac failurePsychiatric illness, including mood or anxiety disordersRespiratory disease, including chronic obstructive pulmonary disease, asthma, or interstitial lung diseaseKidney disease resulting in chronic renal impairment, with creatinine clearance ≤30 mL/minCurrent malignant neoplasm
**Exclusion criteria**
Patients living in or likely to be discharged to a high-level residential care facility for older adultsPatients enrolled in a comprehensive management program upon discharge, for example, a formal rehabilitation program, rehabilitation in the home, heart failure outreach service, chronic obstructive pulmonary disease pulmonary rehabilitation, hospital in the home, or receiving disability or community psychiatric services, including care coordinationPatients followed up through other local health network services providing community outreach, such as patients who are homelessPatients with a current history of illicit drug or alcohol dependence, which may interfere with their ability to engage with the programPatients with palliative intent and likely to have a life expectancy of <6 moPatients due for elective readmission within 2 wk of current hospital dischargeInsufficient cognitive function or English language skills to provide informed consent and complete assessmentsPatients who are found to have been in hospital for >3 wk during the index admission and are not transitional patients

### Identification and Recruitment of Participants

Several procedures to identify and recruit participants for the trial intervention have been incorporated into the study design.

Nursing, medical, pharmacy, and allied health leads and managers; ward staff; and patient flow and bed management meetings will be attended by the research leads and STARnurses to brief staff and explain all aspects of the research and introduce the STARnurses and their role. Emails and flyers will be sent by the research leads to medical, nursing, pharmacy, and allied health leads as well as relevant clinical staff.

Study criteria will be entered into the local electronic medical record to produce a trial list of potential participants. The STARnurses will review the list daily and follow up with relevant treating clinicians. Daily rounds will be conducted at trial wards, and nursing staff will liaise with medical staff to identify patients. Huddles will be attended, and nursing staff will liaise with medical staff to identify patients.

The patient’s clinical team will be consulted first, and if permission is granted, a research team member will then approach the patient. They will be invited to participate in the study, and if they accept, they will be provided with a participant information sheet and consent form for consideration. The patient will then be approached 24 hours later to confirm their willingness to participate. Individual randomization using REDCap will take place following informed written consent [53].

It is acknowledged that participants who provide consent will have multimorbidity and may even be frail, and the collaboration with their multidisciplinary team will be an integral component of the intervention. Therefore, balancing the participant’s agency and self-efficacy and capability with their anxiety and hesitancy will require ongoing discussion between the participant and team members, along with their support.

### Intervention

The intervention involves establishing a transition coordination service led by nursing transition coordinators, who will support transitions and referrals, known as STARnurses. The intervention consists of 4 key phases.

The first phase involves in-hospital screening in which “risk of readmission” screening is conducted during the hospital stay, using the Community Assessment Risk Screen tool [41,42]. Patients who meet the inclusion criteria are invited to participate in the study.

The second phase involves in-hospital baseline assessment, transition planning, and participant goal setting (following participant research and information discussion, acceptance to participate, and consent procedure complete). A detailed inpatient baseline and transition assessment is performed to collaboratively develop personalized goals and a transition action plan. Researchers will use the following tools to assess participants’ transition needs: customized transition nursing assessment [43], Barthel Index [46], Edmonton Frailty Scale [47,48], Kessler Psychological Distress Scale [49], Malnutrition Universal Screening Tool scale [50], and General Self-Efficacy Scale [51]. The participant’s GP or practice nurse will be contacted and receive the transition action plan before the participant’s hospital discharge.

The third phase is posthospital discharge transition coordination. Participants will receive transitional care coordination, with phone calls or telehealth follow-up in the first 48 hours following discharge and then weekly and fortnightly (Figure 1).

**Figure 1 figure1:**
[figure not shown]
Interventions aligned with time points (TPs) of data collection and phone calls. ESAS-r: Edmonton Symptom Assessment System–Revised; TAP: transition action plan.

The fourth phase involves handover to primary care. A multidisciplinary case discussion will occur approximately 4 weeks after discharge in preparation for handover to the GP or practice nurse and other specialist providers. The STARnurse will have a final consultation with the patient after the multidisciplinary case discussion (6-10 wk after discharge) to inform the patient of any outcomes or actions. Handover and written communication are provided to the GP or practice nurse to ensure the participant is stable in the community, and if not stable, follow-up care is required.

In this study, a key adaptation of the TCM is replacing the advanced practice registered nurse home visits with STARnurse telehealth or telephone follow-up. This follow-up is provided according to the intervention protocol (Figure 1). The feasibility of the STARnurse and transition coordinator role and the associated transition service was previously evaluated in an earlier feasibility study [24].

## Results

This project received ethics approval (17554) on June 29, 2023, and it was registered with the Australian New Zealand Clinical Trials Registry on February 15, 2024 (12624000142538). This study commenced on July 1, 2023, with data collection commencing in February 2024; data collection was completed on March 31, 2025. Finalized results are expected in March 2026.

## Discussion

### Anticipated Findings

The primary outcome of this research is decreasing the rate of hospital readmission within 3 months of discharge from the index admission in people with multimorbidity. In a prospective, quasi-experimental TCM study (N=172), improvements in all health status and quality of life measures were observed after intervention compared to before the intervention, and a significant decrease in total number of readmissions (TCM: 45 readmissions vs control: 60 readmissions; *P*<.041) and total hospital days (TCM: 252 d vs control: 351 d; *P*<.032) were observed at 3 months [57].

The secondary outcomes include the cost analysis of the transition service model of care. In a previous study, cost savings were demonstrated in relation to appropriate implementation of the TCM, whereby it was associated with a short-term decrease of US $439 per patient per month in total health care costs at 3 months and cumulative per-patient savings of US $2170 at 1 year (*P*<.037). In a cost comparison study in which the post–acute care costs of 3 care management interventions for hospitalized older adults with cognitive impairment and their family caregivers were compared (N202), the TCM had significantly lower costs than 2 other comparable care management interventions and has been associated with an estimated net savings of US $2972 per individual at 6 months [26].

People with multimorbidity are readmitted to the hospital more, spend more time seeking health care, and often receive fragmented care. When they are discharged from the hospital, they are often readmitted due to poor health care team communication, uncoordinated follow-ups, and not knowing whom to contact when they have symptoms. Supporting these patients as they transition to the community after hospital discharge with an adapted nurse-led TCM intervention will assist them to resume their normal lives more quickly and prevent unnecessary hospital contact.

This study is informed by TCM evidence and an earlier feasibility study [12,39]. Consequently, it represents an additional and focused investigation into a discrete and known area of health service provision. This focus has allowed researchers to refine the intervention to a practical and effective modality. The method responds to previously encountered challenges and locates the participant and their health care team at its center. It is anticipated that patients’ awareness of this approach will encourage their health care agency in a goal-directed and beneficial manner. The previous research was at a single large acute hospital; the sample size was small; and the design omitted the use of comparator groups. These parameters have been addressed in this study, enabling future generalizability of the findings.

### Limitations

Although the power of the research has been addressed through an appropriate cohort number, the 2 hospitals included in this study remain within the same local health network, which could emerge as a limitation later. At this point, an adapted nurse-led TCM is being trialed, posing infidelity to the original model; in addition, people with cognitive impairment have been excluded. However, this research is considered part of an overall plan to eventually embed the transition care model as standard care within the health system; consequently, each research project builds on demonstrated evidence.

Health sectors use diverse electronic record and patient data systems, which can lead to challenges with access and consistency. To address these challenges, this study is a pragmatic one, emphasizing relationship building [46] and fostering regular, consistent communication among the multidisciplinary team, the participants and significant others, and the health sectors as integral components of the nursing interventions.

